### Sample size calculation

An a priori statistical power analysis was conducted in G*Power version 3.1 to determine the optimal sample size having 80% power to detect a small effect size (*f* = 0.15, which corresponds to *d* = 0.30) between the active intervention conditions on the one hand and the control condition on the other. Consequently, the sample size calculation was based on a between-factors repeated measures analysis of variance (ANOVA) with two groups and two measurements (i.e., baseline and post-intervention; T0–T1). A significance level of α = 0.05 was maintained. The effect size was based on data from a previous RCT [20]. Calculations indicated a total of 264 participants will be needed, meaning 88 participants per condition. We assume a Pearson correlation of 0.5 between the outcome variable on baseline and post-intervention (i.e., T0–T1), which explains 25% of the variance of the outcome variable. Therefore, the sample size per group can be reduced by 25%. However, adjusting for an anticipated dropout rate between T0 and T1 of 25% (based on previous data), we will still need 88 participants per condition (*N* = 352). The high dropout rate introduces a risk of bias through selective dropout. However, participants in the previous Featback trial [20] who dropped out during the intervention did not differ from those who did not drop out with regard to ED psychopathology, ED quality of life, comorbid anxiety or depression, age, weight, hours spent online, allocated condition, and duration of their eating problems. Hence, bias because of selective dropout in the current sample is, at least based on these variables, improbable.

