### Statistical analyses

All statistical analyses will be conducted in SPSS version 25 and the R statistical programming environment [85]. A two-tailed significance level of *α* = .05 will be maintained throughout the analyses unless indicated otherwise. All analyses will be conducted according to the intention-to-treat (ITT) approach. This means that all participants who underwent randomization, even those who withdrew from the study or deviated from the protocol, are included in the analyses. For the effectiveness analyses, both ITT and completers analyses will be conducted. A participant is considered a completer when he/she has completed at least five monitoring assessments (i.e., Featback only condition), five support sessions (i.e., expert-patient support only condition), or both (i.e., Featback plus expert-patient support condition).

Missing data will be handled using multiple imputation [86]. Multiple imputations using predictive mean matching will be conducted in the statistical programming environment R [85]. Interactions will be taken into account in the imputation procedure [87]. Multiple imputation methods have several advantages over complete-case analyses or single imputation techniques and are therefore highly recommended [86, 88].

Homogeneity of groups (i.e., between-group differences) will be assessed at baseline (T0) using chi-square tests for categorical variables and ANOVAs for continuous variables. Additionally, homogeneity of variances will be assessed using Levene’s statistic, and non-parametric testing will be used when appropriate.

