Additionally, some limitations of the current study design should be noted. Firstly, participants are allowed to engage in treatment outside of the research for ethical reasons. Although we will control for healthcare appointments during the analyses, methodologically it would be preferable to have all the participants only receive the experimental intervention. Lastly, only online measures will be completed by participants. This limits the diagnostic accuracy, introduces recall bias, and might reduce intervention usage as well. Indeed, we expect a fairly high dropout rate, and missing data might not be at random, which will need to be taken into account when analyzing the data. Nevertheless, the current approach is needed to maintain the low threshold and anonymity of the intervention, making it possible to generalize beyond this study to the real effects of Featback with and without expert-patient support.

The (cost-)effectiveness of Internet-based interventions in combination with expert-patient support for the (early) interventions of individuals with an ED or related symptoms has not been investigated before. Results on this subject will contribute to the delivery of e-mental health and expert-patient support and help to guide individuals with eating problems to the care they need.

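### The protocol says data missing not at random must be taken into account in the analysis, but the only missing-data method it fixes assumes missingness at random

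*Protocol article*

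**What the plan says.** Three sections of the protocol article bear on this point.

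- **Sample size calculation.** Dropout of 25% between T0 and T1 is anticipated. The section first concedes the problem: "The high dropout rate introduces a risk of bias through selective dropout". It then reports that participants in the earlier Featback trial "who dropped out during the intervention did not differ from those who did not drop out with regard to ED psychopathology", nor on several other recorded characteristics, allocated condition among them. Its conclusion, which opens "Hence, bias because of selective dropout in the current sample is", is that such bias is improbable, but only as far as those variables go.
- **Statistical analyses.** All randomized participants are analysed. "Multiple imputations using predictive mean matching will be conducted", with interactions reflected in the imputation model. A completers analysis is added, defined by at least five monitoring assessments, five support sessions, or both, depending on the arm.
- **Discussion.** Among the limitations, after considerable dropout is foreseen: "missing data might not be at random, which will need to be taken into account when analyzing the data". Earlier in the Discussion, multiple imputation is listed as a strength of the design.

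**The concern.** Predictive mean matching fills a missing value with an observed value from a participant who has similar predictors. That is valid if, given those predictors, people who left would have scored like people who stayed. The Discussion says this may not hold and that the analysis must allow for it, but no stated analysis does.

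The assumption is open to doubt in this trial. Participants know their allocation (Design), and all arms may seek outside treatment (Waiting list control). People may leave an active arm because it is not helping and leave the waiting list for other reasons. If so, imputed values would be wrong by different amounts in the arms being compared, and the planned analyses would not show it. What is at stake is whether the result for the first hypothesis (active arms against waiting list on the EDE-Q global score) can be trusted when about a quarter of the T1 outcomes are imputed.

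**Working it through.** **1. The plan's own figures.** Inputs from Sample size calculation: f = 0.15 (d = 0.30), two groups, m = 2 measurements, correlation 0.5, alpha 0.05, 80% power, 25% dropout.

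- Noncentrality for the between-factors repeated measures ANOVA: f² × N × m / (1 + (m − 1) × 0.5) = 0.0225 × 264 × 2 / 1.5 = 7.92. Power is 0.801, so the total of 264 reproduces.
- Dropout step: 88 × 0.75 = 66 per condition, 66 / (1 − 0.25) = 88, and 88 × 4 = 352. This also reproduces.
- Imputed at T1 if dropout is as anticipated: 0.25 × 352 = 88 participants over all arms.

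**2. What each stated element can show.**

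| Element | What it covers | What it leaves open |
|---|---|---|
| Comparison of dropouts in the earlier trial | Recorded variables; dropout during the intervention | Dropout depending on unseen outcomes; dropout between T1 and T5; expert-patient arms |
| Predictive mean matching | Missingness explained by the predictors in the model | Missingness not explained by them |
| Completers analysis | Participants who used the intervention enough | Missing outcomes; no criterion is given for the waiting list |
| Adjustment for baseline variables | Differences on those variables | Missingness depending on later, unseen scores |

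None of these analyses varies the missing-at-random assumption.

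**3. Size at T1 (illustration).** Let p be the share missing, and let delta be the amount, in SD, by which dropouts are truly worse than imputed, for the active (A) and waiting-list (W) arms. The loss of effect is p_A × delta_A − p_W × delta_W. The share p = 0.25 is the plan's and is taken as equal across arms. The deltas are assumptions.

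| delta_A | delta_W | Shift (SD) | Effect left from 0.30 | Share of 0.30 |
|---|---|---|---|---|
| 0.2 | 0 | 0.25 × 0.2 = 0.05 | 0.25 | 17% |
| 0.5 | 0 | 0.25 × 0.5 = 0.125 | 0.175 | 42% |
| 0.5 | 0.2 | 0.125 − 0.05 = 0.075 | 0.225 | 25% |
| equal | equal | 0 | 0.30 | 0% |

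With delta_W = 0, the effect would vanish at delta_A = 0.30 / 0.25 = 1.2 SD. If only the waiting-list dropouts were worse than imputed, the sign would reverse and the planned analysis would understate the benefit.

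**4. Follow-up.** The Intervention effectiveness analyses section tests change from T1 to T5, so an error present at both times partly cancels. With the same delta at both times, active arms only, and an assumed 40% to 50% missing at T5, the net shift is (p at T5 − p at T1) × delta. This runs from (0.40 − 0.25) × 0.2 = 0.03 SD to (0.50 − 0.25) × 0.5 = 0.125 SD. The article gives no T5 dropout figure.

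**The case against.** The strongest reply is that a condensed article commonly names a primary missing-data method and leaves sensitivity analyses to the analysis plan. It would add that the Discussion sentence merely defers the detail. This stands as far as it goes: the absence of a sensitivity analysis would not by itself be a finding. What remains is that the article says the issue must be taken into account, and then fixes methods that do not do so.

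A reader might infer that the Sample size and Discussion sections contradict each other. The text does not support that. The Sample size section admits the risk and confines its reassurance to the variables listed, while the Discussion says only that data might not be missing at random. Both can be true.

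A reader might also dismiss the earlier trial as irrelevant. That goes too far. According to the Background, it shared the Featback-only and waiting-list arms, and it found no difference in dropout by allocated condition. This is useful evidence on how often people leave each arm. It does not show that they leave for the same reasons, and that trial's support came from therapists.

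The size is open to challenge too. The deltas come from no document, and moving only the active arms is the unfavourable case. Multiplying an assumed T5 dropout of 40% to 50% by the same deltas would suggest 0.08 to 0.25 SD, but that ignores that the planned test is of T1–T5 change. Likewise, the 14-month wait bears on follow-up; the main comparison is at 8 weeks.

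**Conclusion.** The point holds in a limited form. The article requires its analysis to allow for data that may not be missing at random, and no analysis it states does this. The Sample size reassurance is hedged and is weaker evidence than its conclusion suggests, but it is not an error of fact.

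Under the assumed deltas of 0.2 to 0.5 SD in the active arms alone, with 25% missing, the T1 effect would move by 0.05 to 0.125 SD, or 17% to 42% of d = 0.30. The figure is an illustration: it falls when both arms are affected and is zero when they are affected equally. The primary analysis can stand, and nothing here shows that it is biased. As written, however, a reader of the results could not tell how far the conclusion depends on the imputation assumption. The change is worth making before outcomes are analysed.

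**What to change.** 1. In Sample size calculation, limit the closing sentence to what was shown: in the earlier trial, dropouts during the intervention resembled other participants on the listed variables. Add that this does not exclude dropout related to unobserved outcomes or dropout after T1, in line with the Discussion.
2. In Statistical analyses, keep predictive mean matching as primary and add a delta-adjusted (pattern-mixture) sensitivity analysis of the EDE-Q global score. Add delta to the imputed values, varied separately in the active and waiting-list arms, for the T0–T1 comparison. For the T1–T5 change, apply delta at both times. Report the delta at which the conclusion on the first hypothesis changes.
3. Choose the range of deltas in advance. The stated reasons for leaving (Attrition follow-up) can inform arm-specific values. They should not be used as general imputation predictors, because participants with observed outcomes have no such reason. Usage counts do not exist on the waiting list, so they cannot serve as a common predictor either.

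The cost is a few lines of text and code on imputations already planned. The downside is that the result may prove fragile.

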### Statistical analyses

All statistical analyses will be conducted in SPSS version 25 and the R statistical programming environment [85]. A two-tailed significance level of *α* = .05 will be maintained throughout the analyses unless indicated otherwise. All analyses will be conducted according to the intention-to-treat (ITT) approach. This means that all participants who underwent randomization, even those who withdrew from the study or deviated from the protocol, are included in the analyses. For the effectiveness analyses, both ITT and completers analyses will be conducted. A participant is considered a completer when he/she has completed at least five monitoring assessments (i.e., Featback only condition), five support sessions (i.e., expert-patient support only condition), or both (i.e., Featback plus expert-patient support condition).

Missing data will be handled using multiple imputation [86]. Multiple imputations using predictive mean matching will be conducted in the statistical programming environment R [85]. Interactions will be taken into account in the imputation procedure [87]. Multiple imputation methods have several advantages over complete-case analyses or single imputation techniques and are therefore highly recommended [86, 88].

Homogeneity of groups (i.e., between-group differences) will be assessed at baseline (T0) using chi-square tests for categorical variables and ANOVAs for continuous variables. Additionally, homogeneity of variances will be assessed using Levene’s statistic, and non-parametric testing will be used when appropriate.

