#### Intervention effectiveness analyses

To investigate the effectiveness of Featback with and without weekly expert-patient support, within-group and between-group effect sizes (Cohen’s *d*) will be calculated (i.e., the effects of time and intervention) using the pooled standard deviation of each group. We are mainly interested in the effect from baseline to post-intervention (T0–T1), but to see if effects are maintained over the short and long term, analyses will be repeated for T1–T3 and T1–T5 respectively.
 To answer the first and main hypothesis that the active interventions (i.e., Featback, expert-patient support, and Featback plus expert-patient support) are more effective than a waiting list in reducing ED symptomatology (i.e., primary outcome EDE-Q global score), the three active intervention conditions will be compared to the waiting list condition. Repeated measures ANOVA will be used for T0–T1 to test this hypothesis. To see if the effects are maintained, these analyses are repeated for T1–T3 and T1–T5. The second hypothesis was that the combination of Featback and expert-patient support would be more effective than Featback or expert-patient support alone. A repeated measures ANOVA with post hoc tests will be conducted to compare T0–T1 differences in ED symptomatology between the four conditions. The post hoc analyses apply the Bonferroni correction for multiple testing. To see if these effects are maintained, these analyses are repeated for T1–T3 and T1–T5.

These confirmatory analyses will be repeated controlling for significant baseline variables (i.e., age, duration of ED psychopathology, number of psychological healthcare appointments). Additionally, the main analyses will be repeated for completers only.

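### The only stated remedy for unequal variances (Levene's test, then non-parametric tests) would not fully protect the 3:1 primary contrast; a Welch-type contrast would, at almost no cost

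*Protocol article*

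**What the plan says.** In the protocol article, Statistical analyses, the paragraph on baseline comparability says that groups will be compared at T0 by chi-square tests and ANOVAs. It then adds that equality of variances will be checked with Levene's statistic "and non-parametric testing will be used when appropriate". It names no trigger, no replacement test and no outcome. The article says nothing else about unequal variances.

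Under Intervention effectiveness analyses, the main hypothesis is tested on the EDE-Q global score: "the three active intervention conditions will be compared to the waiting list condition". The method is given without condition: "Repeated measures ANOVA will be used for T0–T1 to test this hypothesis". The general level is 0.05, two-sided. Under Sample size calculation the comparison is treated as two groups at two times, with 88 participants per condition (352 in all) and 25% dropout expected by T1.

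**The concern.** With two groups and two times, the group-by-time F of a repeated measures ANOVA is the square of the equal-variance t statistic on change. That statistic is sensitive to unequal variances when the groups differ in size, and pooling three arms against one gives a 3:1 split. If the smaller group varies more, the test rejects too often. If the larger group varies more, it rejects too seldom and loses power.

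Moving to a rank test does not solve this. A Mann-Whitney test also needs equal spread to be a valid test of a shift in location, so it leaves part of the problem that Levene's test is meant to detect. It also gives no mean-change coefficient that can be pooled over the planned multiple imputations. What is at stake is whether the primary comparison holds its 5% level and, in the other direction, some of its power.

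**Working it through.** **Inputs from the article.** Two-sided alpha 0.05; 88 per condition; 25% dropout; effect d = 0.30 (f = 0.15); T0–T1 correlation 0.5; three active conditions against one waiting list.

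**The plan's own figure.** For a between-factors repeated measures ANOVA with two groups and two measurements, the noncentrality is f² × N × 2 / (1 + 0.5) = 0.0225 × 264 × 1.333 = 7.92. On 1 and 262 degrees of freedom this gives power 0.801, so 264 is reproduced. Reducing 88 by 25% gives 66, and 66 / 0.75 = 88 per condition, or 352 in all. The primary contrast is therefore 3 × 88 = 264 v 88 randomised, and about 0.75 × 264 = 198 v 0.75 × 88 = 66 observed at T1.

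**Assumption.** The article gives no SD for any arm, so the ratio of the SDs of change is varied.

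**Closed form for the pooled test.** Let r be the waiting-list variance of change divided by the active variance. With 3:1 groups, the estimated variance of the mean difference over its true variance is (3 + r) / (3r + 1). The true size is 2 × [1 − Φ(1.96 × √((3 + r) / (3r + 1)))].

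- Waiting-list SD 1.25 times larger: r = 1.5625; 4.5625 / 5.6875 = 0.802; 1.96 × 0.896 = 1.755; size 7.9%.
- Active SD 1.25 times larger: r = 0.64; 3.64 / 2.92 = 1.247; 1.96 × 1.117 = 2.188; size 2.9%.

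**Simulation.** Normal change scores, equal means, 198 v 66. The gated rule is taken as Mann-Whitney if Levene p < 0.05, otherwise the pooled t. There were 8,000 trials for the rows at ratio 1.25 and 20,000 for the others. The simulation error at 7% with 8,000 trials is √(0.07 × 0.93 / 8,000) = 0.3 percentage points.

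| SD of change | Pooled ANOVA | Rank test | Levene-gated rule | Welch |
|---|---|---|---|---|
| Active 1.41 times larger | 2.0% | 3.0% | 3.0% | 4.8% |
| Active 1.25 times larger | 2.9% | 3.6% | 3.4% | 4.9% |
| Equal | 5.0% | 5.1% | 5.0% | 5.1% |
| Waiting list 1.25 times larger | 8.2% | 6.4% | 7.0% | 5.0% |
| Waiting list 1.41 times larger | 9.5% | 7.5% | 7.6% | 4.9% |

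At 264 v 88 the gated rule behaves almost identically (3.2% and 7.6% for the first and last rows).

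**Source of the distortion.** With equal groups of 88 v 88 and a variance ratio of 0.5 or 2, every procedure stays between 4.9% and 5.2%. The cause is therefore the 3:1 split, and equal-sized pairwise comparisons such as those for the second hypothesis are not affected.

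**Power at a true difference of 0.30, active SD 1.25, waiting-list SD 1.** The true standard error is √(1.5625 / 198 + 1 / 66) = 0.152. Simulated power is 42% for the pooled test and 50% for Welch. With equal variances the figures are 55.3% and 54.7%.

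**How large a ratio is plausible?** Suppose half of the active participants gain 0.60 SD and half gain nothing (mean 0.30). The effect adds variance 0.60² × 0.25 = 0.09, so the active SD is √1.09 = 1.04. Then r = 1 / 1.09 = 0.917; 3.917 / 3.752 = 1.044; 1.96 × 1.022 = 2.003; pooled size 4.5%. A ratio of 1.25 would need an effect SD of √(1.5625 − 1) = 0.75, which is 2.5 times the mean effect.

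**The case against.** The strongest reply is textual. The sentence closes a paragraph on baseline comparability, and the primary ANOVA is specified separately and unconditionally. A reader might infer that Levene's test decides which primary test is run. The article does not say so, and the gated rule simulated above is one construction of an open phrase. This stands. On the baseline-only reading, however, the primary test is the plain pooled-variance ANOVA, which is the more distorted of the two. A condensed article may leave robust variances to an analysis plan that is not shown, so the absence of one is not in itself an error. The point is that the one remedy the article does name would not be adequate for this contrast.

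A reader might also infer that the primary test has a wrong error rate, or take the inflated rates as the expected case. Neither is supported. No SDs are given, and with equal variances every procedure holds 5%. If no intervention changed anyone's outcome, randomisation would give all arms the same distribution and the level would hold. Inflation needs equal mean change with unequal spread, and a more variable waiting list, which nothing in the article predicts. The Background reports that Featback worked best in people with mild to moderate bulimic symptoms. That points at most to more variable change in the active arms, the conservative direction. It concerns one symptom domain, and one of the three active arms receives no Featback.

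Nor would a rank test remove the effect estimate from the report, since Cohen's d is planned separately.

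**Conclusion.** The point holds in conditional form. The stated Levene-then-non-parametric provision, if used for the primary contrast, moves the error rate part of the way back to 5%: at an SD ratio of 1.25, from 2.9% to 3.4% or from 8.2% to 7.0%. Welch stays at about 5% throughout. In the only direction the article gives any reason to expect, the consequence is a conservative test with lower power, not false positives. At ratios near 1.04 nothing material is lost.

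The conclusion rests on the 3:1 pooling, on normal change scores, on assumed SD ratios and on one reading of an open phrase. It does not extend to the second hypothesis. This is a cheap improvement to the wording, not a demonstrated failure of the primary analysis.

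**What to change.** State that the primary active-versus-waiting-list contrast will in all cases be a linear-model contrast of T0–T1 change with heteroscedasticity-robust (HC3) or arm-specific residual variances, or an equivalent Welch-type test, with estimates pooled over the imputations. Say that no Levene test decides the method, and that any rank test is a labelled sensitivity analysis. Limit the existing sentence to the baseline comparisons if that is what is meant.

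Using the same model for the second hypothesis is optional, for consistency. The cost is a sentence or two of wording and, when variances are equal, about half a percentage point of power (54.7% v 55.3%).
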